##### Nursing home admittance

The longer term effect of (time to) nursing home admittance will be analyzed by comparing the intervention and control condition in a Cox’s hazard regression analysis.

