## Background

At present, the number of people living with dementia worldwide is estimated at 47.5 million. This number will increase to 75.6 million in the coming 15 years. Dementia is among the top-5 with the highest burden of disease for persons over 65 years and it belongs to the diseases with the highest burden for informal caregivers. This burden includes physical, emotional and economic pressure. With costs over 604 billion US dollars it is one of the most costly diseases as well [1].

In the Netherlands, about two thirds of persons with dementia is estimated to live at home, but given the impact of the ageing population this number will increase. This is also in line with the preferences of persons with dementia and their informal caregivers [2]. However, living at home with a good quality of life is not easy to achieve.

Dementia is often accompanied by the presence of neuropsychiatric symptoms (NPS), like apathy, agitation, depression, anxiety, and delusions. A systematic review of studies on the course of NPS in community-dwelling patients with dementia found a cumulative prevalence of any neuropsychiatric symptom between 49% and 95% [3]. Delusions, agitation, aberrant motor behavior and apathy are the most common NPS [3]. Neuropsychiatric symptoms not only affect the quality of life of the patient [4], but also result in a higher burden of informal caregivers and a lower quality of their lives [4–6]. NPS are among the most important reasons for nursing home admittance, as they often make the care at home too burdensome [7]. Whereas it is still not possible to treat dementia, dementia care focuses mainly on maintaining quality of life and preventing psychosocial problems [8].

There is evidence that neuropsychiatric symptoms can be prevented or diminished by behavioral interventions [9]. However, it is important that such interventions fit the experiences and life world of persons with dementia well so that they can contribute to the needs of the persons with dementia and their informal caregivers [10].

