##### Inclusion criteria

The main inclusion criterion is (very) mild dementia (Clinical Dementia Rating 0.5 or 1). This will be assessed with the Clinical Dementia Rating Scale [31]. This is a semi-structured interview that is carried out partly with the person with dementia and partly with the informal caregiver. The part for the person with dementia focuses on memory (10 items), orientation (8), and judgment/problem solving (9). The part for the caregiver asks for memory (15 items), orientation (8), judgment/problem solving (6), community affairs (10), home & hobbies (5), and personal care (4). The answers are used to compute a score ranging from 0 = none, 0.5 = very mild, 1 = mild, 2 = moderate to 3 = severe. Participants are included when they score 0.5 or 1. The other inclusion criteria are checked by the researcher during the baseline measurement.

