#### Primary outcome

##### Neuropsychiatric symptoms (NPS)

To assess the effect of the intervention on the primary outcome, neuropsychiatric symptoms, the Neuropsychiatric Inventory (NPI) will be used at all three time points in all participants. The NPI is a reliable and valid measure that is filled out by the primary informal caregiver [41]. The NPI is often used to measure neuropsychiatric symptoms, also in pharmacological and psychosocial intervention studies. The instrument is developed by Cummings (1994) and translated in Dutch by De Jonghe, Borkend and Kat (1997) [42]. The NPI measures the frequency, severity and distress of twelve neuropsychiatric symptoms (Delusions, Hallucinations, Agitation/Aggression, Depression/Dysphoria, Anxiety, Elation/Euphoria, Apathy/Indifference, Disinhibition, Irritability/Lability, Aberrant motor behavior, Sleep and Nighttime Behavior Disorders, and Appetite and Eating Disorders). The frequency (F) is provided on a scale from 0 = never to 4 = daily, the severity (S) on a scale from 0 = not to 3 = severe. The score for each of the twelve symptoms is computed as the frequency multiplied by the severity, resulting in a score ranging from 0 to 12. An FxE score of 4 or higher is seen as clinically relevant symptoms. The twelve FxE scores are added to a total score (0-144) or to four scores of symptom clusters: hyperactivity, psychosis, affective symptoms, and apathy [43].

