#### Personal information

##### Socio-demographics

The following socio-demographics of both the persons with dementia as well as their caregivers are assessed: sex, age, education, marital status and cultural background. These questions are part of the TOPICS-MDS, module General Data [44]. Additionally, the name of their general practitioner is also asked, so they can be informed about the participation in the study.

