#### Randomization check

Chi-square tests and t-tests will be used to check whether the randomization has succeeded in terms of personal information and functioning (TOPICS-MDS), neuropsychological complaints (NPI), caregiver burden (NPI and EDIZ), quality of life of the person with dementia (EQ5D + Cognitive), and quality of life of the caregiver (CarerQOL). When significant differences are found at baseline, we will assess whether these attenuate the outcomes later in time. If that is the case, we will control for these confounding variables in later analyses on the effects of the intervention.

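### The Cox model for nursing home admittance pre-specifies no covariate, and the article's one adjustment rule lets baseline NPI in only after a significance test and CDR not at all

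*Protocol article*

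**What the plan says.** The section Nursing home admittance, under Statistical analyses, gives one sentence: the outcome "will be analyzed by comparing the intervention and control condition in a Cox" hazard regression. No other term is named, and nothing says that other terms are excluded.

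The section Randomization check sets the only general adjustment rule. Baseline tests will "check whether the randomization has succeeded in terms of personal information and functioning (TOPICS-MDS), neuropsychological complaints (NPI), caregiver burden (NPI and EDIZ"), and then quality of life of the person with dementia and of the caregiver. Where a significant difference is found and is judged to affect later outcomes, the rule is: "If that is the case, we will control for these confounding variables in later analyses on the effects of the intervention". CDR is not on that list.

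Three kinds of baseline information bear on admission:

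- **CDR.** It is rated at T0 to decide eligibility: "Participants are included when they score 0.5 or 1". Table 1 files it as an inclusion criterion, outside the TOPICS-MDS modules. The section Randomization describes no stratification by it.
- **NPI.** It is collected from everyone: "the Neuropsychiatric Inventory (NPI) will be used at all three time points in all participants". The Background states that "NPS are among the most important reasons for nursing home admittance".
- **Age.** It is among the socio-demographics in TOPICS-MDS ("sex, age, education, marital status and cultural background"), so the baseline tests can reach it.

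**The concern.** Secondary objective 3 rests on this one model. Two likely predictors of admission, dementia severity and neuropsychiatric symptoms, are measured before randomization in every participant. The plan as written uses the second only if a baseline test is significant, and the first under no stated condition.

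Two things follow. In a Cox model, omitting strong predictors pulls the hazard ratio towards 1 and costs some power even when the arms are perfectly balanced. And the adjustment set is left to depend on the observed baseline data, so a reader cannot know in advance which model will be reported. What is at stake is some precision and the predictability of one secondary comparison. The primary outcome is not affected.

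**Working it through.** **The plan's own figure.** The only sample size in the article is for the primary outcome. For the group-by-time test, λ = f²·N·m/(1−r) = 0.15² × 74 × 3/0.5 = 9.99 with 2 and 144 degrees of freedom. Power is 0.806, so N = 74 reproduces, and 74/0.70 = 105.7 rounds up to 106. No event rate, hazard ratio or power is given for nursing home admittance. Every event rate and hazard ratio below is therefore an assumption.

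**1. Which variables can enter under the stated rule**

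| Variable | Measured at T0 | On the list of baseline tests | Route into the Cox model |
|---|---|---|---|
| CDR | yes | no | none stated |
| NPI total | yes | yes | only if significantly different and related to outcome |
| Age | yes | yes, as personal information | same as NPI |

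**2. What the significance trigger misses.** With 53 per arm, a t-test reaches p < 0.05 at an observed difference of about 1.98 × √(2/53) = 0.38 SD. If NPI carries a hazard ratio of 1.3 to 1.5 per SD (assumed), an imbalance just below that limit goes unadjusted and shifts the crude hazard ratio by 1.3^0.38 to 1.5^0.38, about 11% to 17%.

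**3. Chance imbalance in CDR.** Assume half the participants are CDR 1. The SD of the between-arm difference in that share is √(2 × 0.25/53) = 0.097. The chance of a difference above 10 points in either direction is 2 × [1 − Φ(0.10/0.097)] = 0.30. If CDR 1 carries a hazard ratio of 2 or 3 against CDR 0.5 (assumed), a split of 55% against 45% shifts the crude hazard ratio by (1 + 0.55)/(1 + 0.45) = 1.07 or (1 + 2 × 0.55)/(1 + 2 × 0.45) = 1.11.

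**4. Events.** Schoenfeld's formula, 4 × (1.96 + 0.84)²/(ln HR)², gives 66 events for 80% power at HR 0.5 and 247 at HR 0.7. If 10% to 50% of 106 people are admitted (11 to 53 events), power is 20% to 71% at HR 0.5 and 8% to 25% at HR 0.7.

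**5. Power with and without adjustment.** Simulated trials: 106 people, 18 months of follow-up for each, exponential admission times, true HR 0.5, 1,000 trials per setting. The adjusted model holds condition, CDR, NPI and age. Weak predictors: HR 2 for CDR and 1.2 per SD for NPI and age. Strong: HR 3 and 1.5 per SD.

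| Controls admitted | Events, about | Predictors | Condition only | Adjusted |
|---|---|---|---|---|
| 20% | 16 | weak | 27% | 29% |
| 20% | 17 | strong | 20% | 23% |
| 40% | 34 | weak | 46% | 49% |
| 40% | 34 | strong | 44% | 51% |

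The gain is about 2 to 7 points. A separate simulation gave about 1 to 5 points, for example 13% against 17% at about 12 events and 43% against 48% at about 34. With no treatment effect, the rejection rate was 4% to 5% for the condition-only model and about 5% for the adjusted one.

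**The case against.** The strongest reply is that one sentence in a journal article does not restrict the model to condition. The covariate list of a secondary Cox model is commonly left to a full protocol or analysis plan, and neither is shown. A reader might infer that the model holds condition only. The documents do not support that: the rule under Randomization check applies to later analyses of intervention effects and can bring in NPI, age and daily functioning, the last of which may partly stand in for severity. This part of the reply stands. What remains is that the article does state an adjustment rule, and that rule omits CDR and depends on baseline tests. The article also names its covariates where it intends them: the logistic models for the symptom clusters list condition and baseline status.

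A second reply is that no harm to validity is shown. That is correct. Chance imbalance after randomization is already covered by the standard error, and the type I error of the condition-only model stays near 5%. With SE(log HR) about 2/√events, or 0.50 at 16 events and 0.34 at 34, the CDR shift of 1.07 to 1.11 (0.067 to 0.10 on the log scale) is only about 0.13 to 0.29 standard errors. The drift of the unadjusted hazard ratio towards 1 reflects a marginal rather than a conditional estimand and is not a bias.

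A third reply is that adjustment does not rescue the comparison. This also stands: every simulated scenario remains far below 80% power with or without covariates.

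**Conclusion.** The point holds as a cheap improvement to a secondary analysis. No covariate is pre-specified for the admittance model; CDR cannot enter by any stated route; and baseline NPI, which the article ties to admission, enters only after a significant baseline test.

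The expected benefit is about 1 to 7 points of power at a true hazard ratio of 0.5, over roughly 12 to 34 admissions. It rests on assumed admission rates, an even CDR split, assumed predictor strengths, and complete 18-month follow-up without competing deaths.

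Two stronger conclusions may tempt a reader, and neither is supported. One is that the unadjusted comparison is invalid; it is not. The other is that the article shows the analysis to be short of events. That is plausible across the assumed range, but the article gives no admission rate from which to conclude it.

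**What to change.** In the section Nursing home admittance, state that the Cox model will contain condition, CDR (0.5 or 1) and baseline NPI total as fixed, pre-specified covariates, regardless of the baseline tests, and that the unadjusted hazard ratio will be reported alongside. Say that the test-triggered rule under Randomization check does not apply to this model. Add no covariate conditional on the number of admissions, since that would again let the data choose the model.

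The cost is one sentence; both covariates are already collected at T0. There are two drawbacks. The adjusted hazard ratio is conditional on CDR and NPI, so it answers a slightly different question from the unadjusted one. And with few admissions there are few events per parameter: three parameters at 16 events leave about 5 each (16/3), and at 12 events 4 each (12/3).

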##### Process evaluation

A *content analysis* of twenty randomly chosen Online Life Story Books will be carried out. The analysis focuses on aspects of life stories and autobiographical memories that are known to be related to mental health [54]: the number of memories, the specificity of the memories (memories that refer to events that took place on a single day are considered specific memories), the variance of memories across life domains (family, friends, work, care, and household, leisure, health, historical events), the variance across life phases (childhood, adolescence, young adulthood, middle adulthood, older adulthood) and the variance across media (text, photos, movies, sounds, music). The codes will be quantified into a measure of the complexity of the Online Life Story Book. Descriptive statistics of the complexity measure as well as its correlation with change in neuropsychiatric symptoms between baseline and follow-up will be calculated.

*Qualitative interviews* will be analyzed through story line analysis [55]. Story line analysis allows assessing the most important personal values that are at stake in a story. A qualitative description of its results will be provided.

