#### Making the OLSB

Trained volunteers will support persons with dementia and their informal caregivers. After a first visit to make acquaintance and draw a global time line, the volunteer will visit the participant four additional times in 8–10 weeks. The volunteers follow guidelines that are based on existing scientific and practical insights into reminiscence and dementia [39, 40]. The volunteers are trained to ask for specific memories and to make them as explicit and lively as possible. Together with the person with dementia and his or her caregiver, the volunteer searches for the themes and questions that best match the life story of the participant. The volunteer strives for a variation in themes and life phases across the four visits. After each visit, the volunteer adds memories to the timeline. After the five visits and when the online life book is completed, it will be printed to a tangible version. We expect that it will take approximately 3 months from the first visit of the volunteer to the delivery of the printed book. After the initial construction of the online life book by the volunteer, it remains possible to add memories to the timeline as well as commentaries to memories. The participant will get access for the duration of 1 year. After this year, one gets the opportunity to lengthen the registration for €10,- per year. The necessary guidelines will be made available to the participants. The person with dementia and the caregiver can allow others, like children, families, or friends to contribute to the book.

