#### Process evaluation

The intervention will be evaluated in two ways: a content analysis of Online Story Books and through qualitative interviews. Participants will be asked for renewed informed consent for this part of the study, after they constructed the Online Life Story Book, as they can only then judge whether or not they want to share it with the research team. A content analysis of twenty randomly chosen Online Life Story Books will be carried out.

Qualitative interviews will be conducted using an existing narrative method [52] after the study has been completed. Stakeholders (professionals (care manager, psychologist, coordinator of volunteer work, social worker), volunteers, participants and their informal caregivers) will be asked to provide stories about specific moments before, during, and after the intervention. Each interview will last about 1 h.

Next to the content analysis and interviews, at T1 and T2 participants are asked questions regarding:

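### Correlating book complexity with raw NPI change builds baseline severity into the result; relate complexity to T2 NPI adjusted for baseline NPI and CDR instead (minor)

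*Protocol article*

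**What the plan says.** The Process evaluation paragraph of the statistical analyses says that a "content analysis of twenty randomly chosen Online Life Story Books will be carried out". The coded aspects are the number and specificity of memories and their spread over life domains, life phases and media. Then "The codes will be quantified into a measure of the complexity of the Online Life Story Book", and "Descriptive statistics of the complexity measure as well as its correlation with change in neuropsychiatric symptoms between baseline and follow-up will be calculated". No adjustment is named. The Effects section separates post-intervention from follow-up, so I read follow-up as T2 (6 months).

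Three other statements bear on the point:

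- **Who is included.** Under Process evaluation in the measurements section: "Participants will be asked for renewed informed consent for this part of the study, after they constructed the Online Life Story Book".
- **When the book is finished.** Under Making the OLSB: "We expect that it will take approximately 3 months from the first visit of the volunteer to the delivery of the printed book".
- **Whether it can still change.** The same section says of the online book that "it remains possible to add memories to the timeline as well as commentaries to memories", and that "The participant will get access for the duration of 1 year".

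Table 1 shows that the NPI is collected at T0, T1 and T2 and the CDR at T0.

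**The concern.** Complexity is not randomised. It is observed within the intervention arm, after baseline. Whatever a person's symptom level at entry does to the richness of the book is therefore mixed into any relation with later symptoms.

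A raw change score does not remove that influence. Because change is T2 minus T0, a person who starts high tends to fall and a person who starts low tends to rise, whatever the book contains. A link between complexity and baseline is plausible. Entry spans CDR 0.5 to 1, and the score rewards the number and specificity of memories retrieved. A less affected person may build a richer book and also have less room to improve.

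This is the only quantitative link the article plans between the content of the book and the primary outcome measure. Its sign and size could be misread if part of it is an artefact of the change score.

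**Working it through.** **Inputs**

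- From the Sample size calculation: f = 0.15, alpha = .05, power = .80, 2 groups, 3 measurements, r = .50 between measurements, 74 participants needed, 30% drop-out, 106 included.
- From Process evaluation: 20 books.
- Assumed, because the documents give no figure: the ratio q of the T2 to the T0 SD (1, with a range of 0.8 to 1.2), and the correlation c of complexity with baseline NPI (-0.3 and -0.5).

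**1. The plan's own figure.** For the group-by-time interaction, lambda = f² × N × m / (1 - r) = 0.0225 × 74 × 3 / 0.50 = 9.99, with 2 and 2 × (74 - 2) = 144 degrees of freedom. This gives power 0.806; N = 72 gives 0.795. Then 74 / 0.70 = 105.7, rounded up to 106. Both stated figures reproduce, so r = .50 is a working assumption of the plan itself. The article states no power or precision for the 20-book correlation.

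**2. Baseline against change.** With the T0 SD set to 1, corr(T0, T2 - T0) = (r × q - 1) / sqrt(1 + q² - 2 × r × q).

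- q = 1: (0.5 - 1) / sqrt(1) = -0.50
- q = 0.8: (0.4 - 1) / sqrt(0.84) = -0.655
- q = 1.2: (0.6 - 1) / sqrt(1.24) = -0.359

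**3. Shift in the planned correlation when there is no true link.** Here no true link means that complexity relates to T2 only through baseline NPI. The induced correlation is then c times the value in step 2.

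| c (assumed) | q = 0.8 | q = 1 | q = 1.2 |
|---|---|---|---|
| -0.3 | +0.20 | +0.15 | +0.11 |
| -0.5 | +0.33 | +0.25 | +0.18 |

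A higher NPI is worse, so a positive value means that a richer book appears to go with a worse course. If c were positive, the sign would reverse.

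**4. The same situation after adjustment.** With c = -0.3, corr(complexity, T2) = -0.3 × 0.5 = -0.15. The numerator of the partial correlation given baseline is -0.15 - (-0.3 × 0.5) = 0. The artefact disappears in this model.

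**5. Precision with 20 books (Fisher z).** For an observed r of 0.15: 0.151 ± 1.96 / sqrt(17) = 0.151 ± 0.475, which back-transforms to -0.31 to 0.56. For 80% power, |r| must be tanh(2.802 / sqrt(17)) = 0.59. Adjusting for two covariates changes the half-width on the z scale to 1.96 / sqrt(15) = 0.506. At an estimate of zero, the interval widens from ±0.44 to ±0.47.

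**The case against.** The strongest reply is that this is one sentence in a process evaluation, next to descriptive statistics, with no test or causal model planned. That stands, and it limits the weight of the point. A reader might infer that the result is meant to show how the book works, or that it would steer how the book is rolled out. The article does not say so. Its Discussion makes wider use conditional on the intervention proving effective and leaves implementation to a follow-up project.

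Second, the size rests on an assumed complexity-baseline correlation. This also stands. The volunteer adds the material and aims for variety, and family and friends may contribute, so complexity may depend only weakly on symptoms. At c = 0 there is no shift.

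Third, the shift is small beside the sampling error of twenty books. True, but wide error is no reason to keep an avoidable bias, and the adjustment costs little precision.

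A reader might also infer that the book as it stands at T2 is what will be coded, so that later additions drive the result. The article shows only that a book can grow. It does not say which version is coded, and a condensed article may leave that to the full protocol. Nor does the lack of control books bias the correlation by itself: a course common to everyone leaves a correlation unchanged.

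None of these replies removes the baseline coupling, because the article itself specifies the change score.

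**Conclusion.** The point holds as a minor one. The stated statistic is coupled to baseline NPI at about -0.50 under the protocol's r = .50 and equal SDs. It is therefore shifted by about +0.15 or +0.25 if complexity correlates -0.3 or -0.5 with baseline (0.11-0.20 and 0.18-0.33 for SD ratios of 0.8 to 1.2), with no true link present. The coupling follows from the plan's own figure plus the equal-SD assumption. The complexity-baseline correlation is wholly assumed, in size and in sign.

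Baseline NPI precedes the book, so it is a possible common cause and not a step on the path from book to outcome. Adjusting for it is therefore appropriate. The adjusted value of exactly zero holds only in the simple model above. CDR takes just two values in this trial and is a coarse control for ability, so some confounding may remain. Selection into completed books with renewed consent also remains, and so does poor precision. The sizes of the ability and later-addition effects cannot be derived from the documents. The primary NPI comparison and the sample size are untouched.

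**What to change.** In the Process evaluation paragraph of the statistical analyses, replace the correlation with raw change by a partial correlation, or a regression of T2 NPI on complexity, adjusted for baseline NPI and CDR. Report the estimate with its 95% CI. Describe it as exploratory and non-causal, applying to participants who completed a book and consented again.

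As a minor addition, state that complexity is coded from the version sent to print, so that additions after printing do not enter. This reduces reverse causation but does not remove it: printing is expected about 3 months after the first volunteer visit, hence around T1, and symptoms up to then can still shape the book. The trade-off is that the score no longer reflects later use of the book.

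The cost is a change of wording, one small model and two degrees of freedom. No new visit or measurement is needed.
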